## Background

Adult community-acquired pneumonia (CAP) is an important cause of morbidity and mortality, especially in high-risk groups, both in high- and low-income countries. The burden of pneumococcal pneumonia among adults is not well characterised. Historical estimates were generally based on blood culture results only and therefore underestimated true disease burden [1], or included sputum which may reflect carriage and therefore overestimated burden [2]. Two luminex platform-based multiplex serotype-specific urinary antigen detection (SSUAD) assays have been developed and validated for identification of key *S. pneumoniae* serotypes in urine samples from adults with radiologically-confirmed CAP, which may assist in defining the burden of non-bacteraemic pneumonia [3, 4]. A meta-analysis that included studies utilising additional diagnostics such as the BinaxNOW® *Streptococcus pneumoniae* urine antigen test, attributed 27% of adult CAP to the pneumococcus [1]. This analysis, however, mainly included studies from high-income countries.

Nasopharyngeal pneumococcal carriage is a precursor to pneumococcal disease [5]. Pneumococcal conjugate vaccines (PCVs) protect against colonisation acquisition or density with vaccine-type (VT) and potentially some cross-reactive serotypes, while overall pneumococcal carriage prevalence is only slightly decreased (or unchanged) due to serotype replacement [6]. Nevertheless, reductions in transmission of VT serotypes have resulted in large indirect effects in high-income settings [7] because VTs tend to be more likely to cause disease than replacement serotypes. Indirect or “herd” effects of vaccines refer to the indirect protection of the non-vaccinated population with a reduction in disease or carriage within this group [8].

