To evaluate the association between childhood PCV13 introduction and the trends in incidence of (a) clinical pneumonia or (b) hypoxic pneumonia only (see case definition) in adults 18 years and older in four districts of Ulaanbaatar over a 7 year period (Jan 2015 – Mar 2022).To evaluate the association between childhood PCV13 vaccination (during the early [2019–2020] and late [2021–2022] PCV13 introduction period) and the trends in adult pneumonia (see case definition) in four districts of Ulaanbaatar using the following endpoints: (a) all radiologically confirmed pneumonia, (b) definite pneumococcal pneumonia and (c) VT-pneumonia with a chest radiograph (CXR) consistent with CAP based on clinical assessment at time of hospitalisation.To evaluate the association between childhood PCV13 introduction (during the early and late PCV13 introduction period) and the trends in the detection and density of pneumococci in the nasopharynx of adults admitted with pneumonia.To assess changes in the detection of pneumococcal serotypes (VT and non-vaccine type [NVT]) associated with adult pneumonia in an era of ongoing childhood PCV vaccination.Among adults hospitalised for pneumonia, who have children of vaccine eligible age living in the household, to compare adult cases and controls with respect to having a child in the house who received one or more doses of PCV13 compared with households having all PCV13-unvaccinated children. The case-control comparison will be done for three subgroups: VT (case) compared with NVT pneumococcal pneumonia (control); end-point radiologically-confirmed pneumonia (case) compared with other radiologic findings (control); hypoxic (case) compared with non-hypoxic (control) pneumonia.To evaluate the association between PCV13 introduction in children on the trends in incidence and severity of adult pneumonia associated with viral pathogens (RSV or influenza) in four districts of Ulaanbaatar, during the early and late PCV13 introduction period, for the following endpoints: incidence of severe clinical pneumonia, clinical pneumonia, and radiologically confirmed pneumonia associated with RSV or influenza.

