#### Radiological pneumonia

An adapted version of the WHO definitions for radiological pneumonia in children [36], which accounts for underlying chronic lung disease and significant infiltrates, will be used to diagnose CXR-confirmed disease in adults. Currently, Pfizer is using data from a randomised controlled trial of PCV13 among adults aged ≥65 years in The Netherlands to assess whether the WHO criteria for end-point pneumonia in children are valid for predicting pneumococcal pneumonia in adults. Similar to the definitions used in previous adult pneumonia studies [32], the following three endpoints are proposed:
*Primary end-point pneumonia* will be defined as the presence of focal end-point consolidation (dense/fluffy opacity occupying portion/whole lobe or entire lung, that may or may not contain air-bronchograms) or pleural effusion in the lateral pleural space spatially associated with a pulmonary parenchymal infiltrate or if the effusion obliterated enough of the hemithorax to obscure an opacity.*Other infiltrates* will be defined as other patchy interstitial infiltrates without a pleural effusion or focal end-point consolidation. This will be a separate category as it may be difficult to confirm as acute lung disease in patients with a history of underlying chronic lung disease.*CXR-negative* will be defined as patients with no consolidation, infiltrate or effusion.

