#### Nested case-control study

This substudy will only include adults residing in households with children eligible to receive PCV13. Vaccine eligibility will be based on the relevant district vaccine introduction timelines. We will confirm household level vaccination data, obtained by verbal report, using clinic or electronic immunisation records if available. Children eligible to receive PCV13, who are identified as unvaccinated, will be referred to their local health centre for catch-up according to local guidelines.

When we identify an adult, who is hospitalised for pneumonia and who has children of vaccine eligible age living in the household, we will seek to enrol the adult and their household in the case-control study. We then conduct three separate case-control analyses (defined below) with respect to having any child in the house who received one or more doses of PCV13 compared with households having all PCV13-unvaccinated children.

The case-control comparison will be done for three endpoint-based subgroups.
Among adults hospitalised with pneumonia and with a CXR consistent with CAP based on clinical assessment at time of hospitalisation, VT pneumococcal pneumonia (case) compared with NVT pneumococcal pneumonia (control) based on serotype-specific urine antigen assays.Among adults hospitalised with pneumonia and with a CXR obtained, those with findings meeting adapted World Health Organization (WHO) paediatric radiological criteria (case) compared with those who have any other radiologic finding (control). This analysis is based on the assumption that pneumococcal pneumonia is more likely to have WHO endpoint consolidation CXR findings than non-pneumococcal pneumonia.Among adults hospitalised with pneumonia and with pulse oximetry performed, those with hypoxia (case) compared with those without hypoxia (control). This analysis is based on the assumption that pneumococcal pneumonia is more likely to be hypoxic than non-pneumococcal pneumonia.

These analyses will be controlled for relevant confounders, such as age and housing type.

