**Fig. 1 Fig1:**
[figure not shown]
Schematic diagram of study design and timelines

The outcome variable for this analysis will be monthly district-level counts of severe clinical pneumonia. The IRR will be estimated using a mixed effects Poisson loglinear regression model (or a negative binomial model if there is over-dispersion) fitted to monthly counts, with log-transformed population denominators included as an offset. The model will include a fixed effect for PCV13 (indicator variable for PCV13 introduction which will depend on the district as PCV13 introduction was staggered), a fixed effect for time (time since study commencement in months) to account for temporal trends, and a random effect for district. The PCV13 term will be exponentiated to obtain the incidence rate ratio for the vaccine effect. This model assumes that there is uniform vaccine impact across the districts. Sensitivity analyses will explore whether the vaccine impact differs across districts and will include seasonality and employ changes in vaccine coverage as opposed to fixed PCV13 effects. A subgroup analysis will explore rate changes in different age groups (18–25, 26–45, 46–65 and > 65 years). We will also do a sensitivity analysis with a 1 year “lag period” for indirect PCV effect (as we don’t expect the indirect effect to be instantaneous).

For the secondary pneumonia endpoints, no pre-PCV13 radiological and urine data are available. Consequently, we will explore trends over time in the post-PCV13 introduction period, incorporating district and time since PCV13 introduction.

We will conduct a nested case-control analysis (“test-negative design” [46]) to measure the indirect PCV13 vaccine effectiveness among adults living with children eligible to be vaccinated with PCV13. The model will account for district and time since vaccine introduction. We will compare the odds of receiving PCV13 among household children between cases and controls, defined as: 1) adults with vaccine type (cases) versus non-vaccine type pneumonia (controls), 2) among adults who had a CXR, WHO defined radiological confirmed pneumonia (cases) versus no radiological pneumonia (controls) and 3) among adults who had pulse oximetry, hypoxic (cases) versus non-hypoxic (controls) pneumonia.

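### The chest X-ray and hypoxia case-control contrasts carry the label of indirect vaccine effectiveness, but they are proxy comparisons biased toward the null, and the X-ray control group is described in two ways

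*Protocol article*

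**What the plan says.** The Statistical analysis plan section (text after Fig. 1) calls the nested case-control study a test-negative design, gives its purpose as "to measure the indirect PCV13 vaccine effectiveness among adults living with children eligible to be vaccinated with PCV13", and then names three contrasts.

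- **Serotype:** "adults with vaccine type (cases) versus non-vaccine type pneumonia (controls"). The Nested case-control study section adds that status comes from serotype-specific urine assays.
- **CXR:** "WHO defined radiological confirmed pneumonia (cases) versus no radiological pneumonia (controls"). The Nested case-control study section instead has end-point cases "compared with those who have any other radiologic finding (control"), and Study objectives has "end-point radiologically-confirmed pneumonia (case) compared with other radiologic findings (control").
- **Hypoxia:** "those with hypoxia (case) compared with those without hypoxia (control"), with no condition on any urine or serotype result.

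For the last two, the Nested case-control study section gives one justification each: pneumococcal pneumonia is assumed more likely than other pneumonia to show end-point consolidation, or to be hypoxic.

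The Radiological pneumonia section has three CXR classes: primary end-point, other infiltrates and CXR-negative. Of other infiltrates it says: "This will be a separate category as it may be difficult to confirm as acute lung disease". The Definite pneumococcal pneumonia section, by contrast, accepts any infiltrate compatible with CAP as radiographic confirmation.

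**The concern.** A test-negative odds ratio can be read as VE when cases have the disease the vaccine prevents and the exposure does not change the risk of being a control. The serotype contrast is built that way. The CXR and hypoxia contrasts are not. Their stated rationale is that pneumococcus is relatively more common among cases. That concerns all pneumococci rather than the vaccine types, and it neither removes non-VT disease from the cases nor VT disease from the controls.

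If one minus the odds ratio from these contrasts is reported as indirect VE, a small or null value could be taken as evidence against indirect protection even where protection is substantial. The authors intend the results to guide paediatric and adult immunisation policy, so the label matters.

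The CXR wording is a separate problem. Patients with other infiltrates are controls under Study objectives and Nested case-control study. Under the Statistical analysis plan wording they may be excluded, depending on how radiological pneumonia is read.

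**Working it through.** The article gives no expected VE, sample size or power for this substudy, so there is no stated figure to reproduce.

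**1. Formula.** Let *a* and *b* be the VT shares among unexposed cases and controls, and *v* the true indirect VE against VT pneumonia. Assume no effect on non-VT disease and no confounding. Exposure multiplies the case rate by (1 − *av*) and the control rate by (1 − *bv*), so

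OR = (1 − *av*) / (1 − *bv*), and apparent VE = 1 − OR.

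A contrast with only VT cases and no VT controls (*a* = 1, *b* = 0) returns *v* exactly.

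**2. Simple example** (*a* = 10%, *b* = 5%, *v* = 50%, all assumed). OR = 0.95/0.975 = 0.974, apparent VE 2.6%. With every VT patient removed from the controls (*b* = 0), it is 1 − 0.95 = 5.0%.

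**3. VT shares from the article.** The Discussion cites 4.6% (PCV13 serotypes, US surveillance) and 12.2% (only the additional PCV13 serotypes, UK adult CAP). The Background cites 27% for all pneumococci, used here as a ceiling. Not in the documents, and assumed: the odds ratio linking VT status to being a case is 2 to 5, and cases are 20% or 50% of patients. For each combination *a* and *b* are solved so that the overall VT share matches.

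| Overall VT share | Apparent VE, true 30% | Apparent VE, true 50% | Apparent VE, true 80% | True 50%, VT-free controls |
|---|---|---|---|---|
| 4.6% | 0.9–2.9% | 1.5–4.8% | 2.4–7.8% | 3.0–6.1% |
| 12.2% | 2.2–6.7% | 3.8–11.4% | 6.2–18.7% | 7.9–14.9% |
| 27% | 4.3–11.3% | 7.5–19.7% | 12.8–33.8% | 16.9–27.7% |

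With no enrichment (odds ratio 1), apparent VE is 0% at any true VE.

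**4. Where the loss arises.** Take share 12.2%, enrichment 5, cases 20%: *a* = 0.298, *b* = 0.078. At *v* = 50%, OR = (1 − 0.149)/(1 − 0.039) = 0.851/0.961 = 0.886, apparent VE 11.4%. With clean controls it would be 0.298 × 0.5 = 14.9%. Non-VT disease among cases takes it from 50% to 14.9% (35.1 points); VT disease among controls takes a further 3.5 points.

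**5. Could such values be told from zero?** As a best case, suppose all of the estimated 3500 prospective cases (Discussion) lived with an eligible child, split evenly on case status and exposure, giving 875 per cell. SE(log OR) = √(4/875) = 0.0676, and 1.96 × 0.0676 = 0.1325. The expected 95% interval excludes 1 only if OR is below exp(−0.1325) = 0.876, an apparent VE above 12.4%. At true VE 50%, every value in the 4.6% and 12.2% rows is below that. The substudy takes only adults living with eligible children, so its precision will be lower.

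**6. The CXR control definition.** Assume VT shares of 20% (end-point), 10% (other infiltrates) and 3% (CXR-negative), the last two classes equally common, and *v* = 50%:

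- controls other infiltrates only: 1 − 0.90/0.95 = 5.3%
- controls both classes (*b* = 6.5%): 1 − 0.90/0.9675 = 7.0%
- controls CXR-negative only: 1 − 0.90/0.985 = 8.6%

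The choice moves the estimate by a few points.

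**The case against.** The proxy basis of the two contrasts is disclosed, and Study objectives and Nested case-control study describe only a comparison of exposure between groups. The VE wording comes from one introductory phrase, no sentence says that one minus the odds ratio will be reported as VE for each contrast, and a separate analysis plan holds further detail. This is fair and limits the point. Still, the phrase governs all three contrasts, and nothing in the article states what the proxy assumption does to the size of the estimate.

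On the CXR controls, the WHO qualifier in the statistical section allows a reading in which anyone not meeting end-point criteria is a control, which would agree with the other two sections. That reading is possible, but the broader sense of radiographic confirmation under Definite pneumococcal pneumonia points the other way, so the text should settle it.

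A reader might also infer that the serotype contrast overstates VE because NVT disease rises through replacement. The documents do not support this. The Background sentence, "overall pneumococcal carriage prevalence is only slightly decreased (or unchanged) due to serotype replacement", is about carriage, and the article adds that vaccine types tend to be the more pathogenic. A population-wide rise in NVT disease would affect exposed and unexposed households alike, and the model is to account for district and time since introduction. Bias would need NVT disease to differ by household exposure within district and time. That is a conditional risk which the article does not quantify.

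**Conclusion.** The point holds for the CXR and hypoxia contrasts: their odds ratios do not estimate indirect VE and are pulled toward the null. At the VT shares the Discussion cites, a true VE of 50% would appear as about 1.5% to 11%. These sizes rest on the assumed enrichment and case fractions and on VT shares from other countries; the Background says there are no adult serotype data for Mongolia.

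Three stronger readings go too far. The result need not be near zero: at the 27% ceiling with the strongest enrichment, true VE of 50% to 80% would show as about 20% to 34%. VT disease among controls is not the main cause, and cleaning the controls alone would not cure the problem. The CXR mismatch does not produce a null result; it is a consistency defect with a small numerical effect.

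This concerns a secondary substudy, not the primary incidence analysis, but it should be corrected because it governs how a null result would be read.

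**What to change.** 1. In the Statistical analysis plan section, reserve the term indirect vaccine effectiveness for the serotype-defined contrast. Describe the CXR and hypoxia contrasts as exploratory odds ratios for proxy endpoints, state the expected attenuation, and say that a null result there is not evidence of no indirect protection.
2. Use one CXR definition in Study objectives, Nested case-control study and Statistical analysis plan: cases are primary end-point pneumonia; controls are other infiltrates plus CXR-negative. Add a sensitivity analysis with CXR-negative controls only.
3. Optionally, beside VT versus NVT, report a sensitivity comparison whose controls are all urine-tested pneumonia patients negative on UAD1, the assay for the 13 PCV13 serotypes. This is a design choice rather than the correction of an error.

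The cost is revised wording and one or two extra model fits. No sampling or testing beyond what is planned is needed.

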## Discussion

We have designed an active hospital-based adult pneumonia surveillance programme to evaluate the indirect impact of childhood PCV13 vaccination on different adult pneumonia endpoints, determine the incidence of all cause pneumonia in Mongolia in adults 18 years and older, and determine the changes in pneumococcal serotypes causing adult disease over time. This study will collect over 4 years of retrospective pneumonia data (over 4500 cases) and 3 years of prospective pneumonia data (an estimated 3500 cases).

Childhood PCV13 programmes provide indirect protection to adults through reductions in carriage and transmission, in turn enhancing the vaccine’s public health value [47, 48]. Such a full public health accounting is particularly important for high burden lower-income countries that are graduating from Gavi, The Vaccine Alliance support. In addition, it is important to collect data evaluating potential limitations of paediatric PCV13 programs in protecting adults. Invasive pneumococcal disease surveillance data from the UK has demonstrated that some vaccine serotypes continue to circulate and cause disease, with increasing incidence, despite a robust paediatric immunisation program [49]. Similarly in adults with CAP in the UK, 12.2% of disease was due to the additional PCV13 serotypes (predominantly serotype 3) and 15.1% due the additional PPSV23 serotypes [50]. A prospective surveillance study in the United States which recruited adults from 21 acute care hospitals from October 2013 to September 2016, detected PCV13 serotypes in 4.6% of all patients and 4.2% of elderly patients ≥65 years with radiologically-confirmed pneumonia [51]. Over the study period a small decrease was seen in PCV13 serotypes in those groups recommended to receive PCV13 (≥65 years and those with high risk conditions), but not in the groups where PCV13 was not recommended routinely [51]. Other studies have demonstrated some reductions in all-cause or clinical pneumonia from direct PCV13 immunisation of older adults despite long-standing paediatric PCV programs [52, 53]. If such results are duplicated in Mongolia it will inform decision makers on whether PCVs, including planned 15 and 20-valent vaccines, will likely have a role in directly protecting adults.

Previous studies have shown increases over time in the indirect effect of childhood vaccination with PCV7 and PCV13 on adult invasive pneumococcal disease [54] and pneumonia [15]. Indirect impact is not only related to time since vaccine introduction, but it is also affected by other factors such as vaccine coverage and timing. The point at which indirect effects are observed in different settings may therefore be variable. Vaccine introduction was completed in the study districts in 2018 and we therefore assigned 2019/2020 as the early PCV introduction period for comparison to the last 2 years of the study 2021/2022.

### Study strengths

Documenting the impact of PCVs in Asian countries is limited by only a few sites having denominator-based surveillance for invasive disease or pneumonia and the ability to accurately investigate and document pneumonia cases. Our active hospital-based surveillance as well as population district level denominators will allow us to determine the incidence of adult pneumonia in Ulaanbaatar, Mongolia and the indirect impact of paediatric PCV13 use on adult outcomes. The sampling and laboratory methods used are consistent with other research studies that have described nasopharyngeal carriage in adults [55]. We also used gold-standard molecular methods to detect pneumococcus in the nasopharynx [42]. The use of the SSUAD assay, which detects PCV13 and PPSV23 VT pneumococcal polysaccharides in the urine of adults with suspected pneumonia, will allow us to determine the indirect effect of PCV13 on PCV13 VT non-bacteraemic pneumococcal CAP in adults.

PCV13 was introduced in a phased manner (at district level) in Mongolia. This will allow for between and within district comparisons and allow us to explore heterogeneity in effects between districts and possibly account for some unmeasured confounders.

Our study collects data on other factors which may influence trends in respiratory disease, as well as a control condition, and incorporates different study designs, which will help us to interpret the changes over time in adult pneumonia following PCV introduction.

### Study limitations

While our study includes four districts containing over 70% of Ulaanbaatar’s population, we did not include five of the city’s districts. Therefore, our findings may not be applicable to rural areas of the country. We only have 1 year of data pre-PCV13 introduction for all districts, however due to the phased introduction of the vaccine this period is extended in some districts. We have included both retrospective and prospective surveillance data which may potentially differ; however a standard clinical medical record was used in the district hospital sites over the entire period from 2015 with the same available clinical information for both periods, reducing the risk of discrepancies. We do not have pneumococcal carriage data for the retrospective period and have therefore chosen clinical endpoints as our primary study objective. The 2015/16 measles outbreak and annual variations in influenza and RSV cases may impact pneumonia outcomes; however, as we have administrative data available for both, we plan to incorporate this information into the descriptive interpretation of study results.

The adult surveillance programme in Mongolia will provide data to help guide paediatric and adult PCV immunisation policy in the country. It will contribute to the incomplete evidence available on the burden of pneumococcal pneumonia in adults in low resourced countries, particularly in the Asia-Pacific region. The study is one of the few active population-based pneumonia surveillance programmes evaluating the indirect impact of PCV in a resource-limited setting. With increasing introduction of PCV in low-resourced settings, the methods, experiences and lessons learned from our study may be used to guide the development of such systems in other countries.

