#### Clinical information collected on other relevant interventions and control condition

Ongoing information is collected on any changes in clinical practice or policies affecting pneumonia admissions instituted over the study period. This includes changes in antibiotic policies, antibiotic prescription practices, annual influenza vaccination campaigns (number of vaccine doses dispensed and coverage by age group) and changes in admission criteria.

There was a large nationwide measles outbreak in Mongolia which began in March 2015 and had two waves, March to September 2015 [38] and October 2015 to June 2016 [39]. A total of 49,908 suspected cases were reported, and 33,947 cases were confirmed. During the first wave, 9671/14,010 (69%) cases occurred among adults ≥15 years and 11,346/19,937 (57%) in the second wave [39]. We will also need to account for the potential changes in hospital admissions due to the ongoing COVID-19 pandemic and related public health interventions from 2020. To account for changes in hospital admissions due to the ongoing COVID-19 pandemic, we are collecting data on lockdown and other public health restrictions, COVID vaccination rates and vaccination status for admitted pneumonia cases. In addition, all adult respiratory cases are tested for SARS-CoV-2 on admission to hospital using rapid antigen testing and confirmation by PCR. Only SARS-CoV-2 negative pneumonia cases are enrolled into the surveillance programme.

To ascertain whether health-seeking behaviour and admission practices may have changed between the retrospective and prospective periods, admissions for two “control” conditions, cardiovascular and renal disease, will be collected over the entire study period (2015–2022) at all four hospitals for all adult patients. Weekly (prospective) or monthly (retrospective) numbers will be collected by age group and diagnosis category (for cardiovascular disease: ischaemic heart disease, heart failure, hypertension, cardiomyopathy, heart valve disease, vasculitis and other cardiovascular disease; for renal disease: pyelonephritis, renal failure, cystitis, glomerulonephritis and other renal disease).

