##### Statistical analysis plan

The primary analysis endpoint will be the change in severe clinical pneumonia incidence rate ratios (IRR) comparing the pre- and post-vaccine periods over 87 months in all four districts (Songinokhairkhan and Sükhbaatar with 17 months pre-PCV and 70 months post-PCV; Bayanzürkh with 30 months pre-PCV and 57 months post-PCV; and Chingeltei with 38 months pre-PCV and 49 months post-PCV). Retrospective data from 2015 will be used to contribute to pre-vaccine case numbers for the primary outcome. See Fig. 1 showing the schematic study timelines.

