Numbers of cases hospitalised with cardiovascular or renal disease in the four district hospitals will be collected from 2015 to 2022 as two separate “control” conditions to help determine whether changes over time are related to secular trends or vaccine effects. We will include the control condition in the model for severe clinical and clinical pneumonia as a covariate. We will have an “uncontrolled” model as the main analysis, and a “controlled” model as a sensitivity analysis.

Chi-square tests will be used to evaluate changes in PCV13 and non-PCV13 serotypes over time, comparing the proportions of both identified in year one to year three, for each age group.

An interim analysis will be conducted for the primary clinical outcome in December 2020 and will be conducted in the same way as the final analysis except for a shorter follow-up time (71 months). The final analysis, which will include all primary and secondary objectives as well as laboratory data (nasopharyngeal swabs and urine), will be conducted once data collection, data cleaning and laboratory analysis has been completed - planned end of 2022.

A separate detailed statistical analysis plan including details related to the secondary analyses, nested case-control study and changes to model assumptions considered for sensitivity analyses has been approved by the study statisticians.

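### The primary model has no term for the 2015-16 measles outbreak or the COVID-19 period, which fall on opposite sides of PCV13 introduction, so the incidence rate ratio can be biased

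*Protocol article*

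**What the plan says.** The Statistical analysis plan section of the protocol article lists the terms of the primary model: a PCV13 term ("indicator variable for PCV13 introduction which will depend on the district as PCV13 introduction was staggered") and "a fixed effect for time (time since study commencement in months) to account for temporal trends, and a random effect for district". Seasonality, vaccine coverage in place of the step, district-specific effects and a one-year lag are sensitivity analyses. So is adjustment for the cardiovascular and renal control conditions: "We will have an “uncontrolled” model as the main analysis, and a “controlled” model as a sensitivity analysis".

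The protocol itself identifies both disturbances. The section on other relevant interventions and the control condition reports: "There was a large nationwide measles outbreak in Mongolia which began in March 2015 and had two waves, March to September 2015". It gives a second wave from October 2015 to June 2016, with 69% and 57% of cases in the two waves aged 15 or over. The same section says "We will also need to account for the potential changes in hospital admissions due to the ongoing COVID-19 pandemic", lists the data being collected on restrictions and COVID vaccination, and limits enrolment to SARS-CoV-2-negative cases. No sentence says how any of this enters the model.

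Study limitations accepts that measles and annual influenza and RSV variation may affect pneumonia outcomes, and handles them this way: "as we have administrative data available for both, we plan to incorporate this information into the descriptive interpretation of study results". In that sentence the two items are measles and influenza/RSV. COVID-19 is not among them.

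**The concern.** Both periods are aligned with vaccine exposure. One raises the early, mostly pre-PCV level, if measles adds severe pneumonia admissions. The other probably lowers the late, wholly post-PCV level, through restrictions and changed care-seeking. Testing out SARS-CoV-2-positive cases does not remove that second effect.

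A single slope cannot follow a bump at the start or a drop at the end. An early bump looks like a fall at introduction, which imitates a vaccine benefit. A late drop steepens the fitted slope, and the PCV13 coefficient rises to compensate, which hides a benefit. The primary IRR is meant to inform paediatric and adult PCV policy, and the study is powered for a 20% decrease, so errors of that order matter.

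**Working it through.** **The plan's own figure.** Sample size estimation states 92% power for 9.8 to 7.8 per 10,000 person-years. The stepped-wedge variance formula, with one effect per month, 4 districts, 87 months, 13,271 person-years per district-month and intra-district correlation 0.2, gives about 92% at one-sided 0.05 using the mean rate, and 86 to 90% at two-sided 0.05. Sidedness is not stated. The protocol gives no figure for bias.

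**Overlap.** Number the months from January 2015. The protocol gives "Songinokhairkhan and Sükhbaatar with 17 months pre-PCV and 70 months post-PCV", with 30 and 38 pre-PCV months in the third and fourth districts.
- Measles, March 2015 to June 2016, is months 3 to 18. That is 15 of the 17 pre-PCV months in two districts (June 2016, month 18, is their first post-PCV month), 16 of 30 in the third and 16 of 38 in the fourth.
- COVID-19 is given only as from 2020. I assume February 2020, so months 62 to 87: 87 - 61 = 26 months. All follow month 38, so all are post-PCV everywhere.

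**Model fitted.** log E(Y) = log N + district + β·X + γ·t, where X = 1 once t exceeds 17, 17, 30 or 38, and IRR = exp(β). It is fitted to expected counts with no vaccine effect: 13,271 × 9.8/10,000 = 13.0 cases per district-month, multiplied by m in months 3 to 18 and by c from month 62. District terms are fixed; a random intercept gave the same values (0.873 against 0.872, and 1.166 in both).

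**Results (true IRR 1; m and c are assumptions).**

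| Measles | COVID-19 | IRR, linear time |
|---|---|---|
| +10% | none | 0.95 |
| +20% | none | 0.91 |
| +30% | none | 0.87 |
| none | -20% | 1.10 |
| none | -30% | 1.17 |
| none | -40% | 1.24 |
| +20% | -20% | 1.00 |
| +30% | -30% | 1.01 |
| +10% | -30% | 1.11 |
| +10% | -40% | 1.18 |

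Moving the COVID-19 start between January and April 2020 barely changes the -30% result (1.16 to 1.17). Under the null, measles at +30% alone gives a significant decrease 77% of the time. With a true IRR of 7.8/9.8 = 0.796, COVID-19 at -30% alone gives 0.92 and cuts power from 98% to 28%.

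**Planned sensitivity analyses.** Seasonal terms leave 0.87 (measles +30%) and 1.17 (COVID-19 -30%). The one-year lag brings measles +30% to 0.98 but leaves COVID-19 -30% at 1.10.

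**Remedies.** One indicator per period, or calendar-month effects, returns 1.00 in every row. Precision at IRR 0.796 follows from power = Φ(0.228/SE - 1.96):
- linear time: SE 0.057, power 98%
- two indicators: SE 0.067, power 93%
- calendar-month effects: SE 0.075, power 86% (84% for an IRR of exactly 0.80)

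**The case against.** The strongest reply has four parts.

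1. **The sizes are assumed, and the shocks pull in opposite directions.** This stands. A reader might infer a bias of 10 to 25% either way. The documents do not support that. They give no shock sizes, the downward range shown is 5 to 13%, and an IRR of 0.75 would need measles at about +71%. Equal and opposite shocks of 10 to 30% leave a net bias of 1% or less. Such cancellation would be luck, however, and could not be verified from the fitted IRR.

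2. **The word linear does not appear.** This also stands. The wording is "a fixed effect for time (time since study commencement in months) to account for temporal trends", for which a linear term is the natural reading. The power formula uses month effects, under which shocks common to all districts cause no bias. It reaches 92% only at one-sided 0.05, so it does not settle what the analysis model intends.

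3. **COVID-19 may be dealt with in the separate analysis plan.** A reader might infer that COVID-19 is ignored. It is not: the protocol commits to account for it and collects data to do so. But the article sets out the terms of the main model and calls it uncontrolled. It describes the separate plan as covering secondary analyses, the case-control study and changes of assumption for sensitivity analyses. For measles there is no such silence, because descriptive handling is stated.

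4. **Month effects as the primary model would be costly.** A reader might infer that they are the obvious replacement. All four districts are exposed after month 38, so concurrent exposed and unexposed districts exist only in months 18 to 38. The protocol expects the indirect effect to be delayed. A true 20% reduction starting 12 months after introduction is returned as 0.99 with month effects, against 0.96 with linear time. This objection stands, and it is why month effects are proposed only as a sensitivity analysis.

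**Conclusion.** The point holds in qualified form. Followed as written, with time linear, the primary model can attribute part of the measles and COVID-19 disturbances to PCV13. Direction and net size cannot be determined from the documents. Over the assumed ranges shown, the IRR under no effect runs from 0.87 (measles alone) to 1.24 (COVID-19 alone), with joint cases between 1.00 and 1.18. The larger risk is therefore a masked benefit where COVID-19 dominates.

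This rests on a linear time term, multiplicative shocks constant within each period and common to the four districts, a February 2020 start, and Poisson variation without over-dispersion.

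**What to change.** In the primary model of the Statistical analysis plan section:

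- Add one indicator for March 2015 to June 2016 and one for the COVID-19 period, with its start date fixed in advance. Where available, district-level monthly measles counts and restriction data can replace them.
- State whether time is linear or categorical.
- Amend Study limitations so that measles is no longer left to description alone.

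As sensitivity analyses, run:

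- calendar-month fixed effects, paired with the planned one-year lag because of the delay problem above;
- a data cut before 2020 that keeps the measles indicator. At 60 months, linear time alone still gives 0.91 for measles +30%; with the indicator it gives 1.00, with SE about 0.073.

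The cost is wording, plus the rise in SE from about 0.057 to 0.067 and the fall in Poisson power from about 98% to 93%. Over-dispersion would lower both power figures. Two limits remain. Indicators remove only a level shift shared by all districts. They also do not cure a delayed effect: the 12-month-delay example returns 0.97 with two indicators, so the lag analysis is needed in any case.
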